| Number of Participants with Rationale (if no Power Analysis conducted): | 
We plan to include 6000 women in the study. Assuming a prevalence of HPV infection of 20%, 1200 participants will be HPV+.
 
 
- Among the awaited 1200 HPV+ women, 120 will have CIN2+ lesions (assuming a prevalence of CIN2+ of 10% among HPV+ women). Assuming a 20% drop-out rate, 96 cases of CIN2+ will be analyzed to determine the sensitivity of VIA (expected around 60%) with a precision of +/- 9.8%.
 
- Among the awaited 1200 HPV+ women, 1080 will not have CIN2+ lesions. With a drop-out rate of 20%, 864 cases of non-CIN2+ will be analyzed to determine the specificity of VIA (expected around 50%) with a precision of +/- 3.3%.
 
 |
| Study Duration:                                                         | 72 months                                                                                                                                                                                                                                                                                                                                                                                                                                                                                                                                                                                                                                                                                                            |
| Study Schedule:                                                         | 
Month Year of First-Participant-In (planned): September 2018
 
Month Year of Last-Participant-In/Out (planned): September 2024
                                                                                                                                                                                                                                                                                                                                                                                                                                                                                                                                                                           |
| Principal Investigator:                                                 | 
[name]
Division of Cooperation
Ministry of Health
[contact]
Email: [contact]
                                                                                                                                                                                                                                                                                                                                                                                                                                                                                                                                       |
| Study Centre(s):                                                        | The project will take place in Dschang District Hospital                                                                                                                                                                                                                                                                                                                                                                                                                                                                                                                                                                                                                                                             |
| Statistical Analysis incl. Power Analysis                               | We will determine the sensitivity, specificity, positive and negative predictive values of VIA/VILI to detect CIN2+ among HPV-positive women. Histology will be used as gold standard. All these will be done using a 95% confidence interval.                                                                                                                                                                                                                                                                                                                                                                                                                                                                       |
| GCP Statement:                                                          | This study will be conducted in compliance with the protocol, the current version of the Declaration of Helsinki, the ICH-GCP as well as all national legal and regulatory requirements.                                                                                                                                                                                                                                                                                                                                                                                                                                                                                                                             |

|                                             |                                                                                                                                                                                                                                                                                                                                                                                                                                                                                                                                                                                                                                                                                                                                                                                                                                                                                                                                                                                                                                                                                                                                                                                                                                                                                                                                                                                                                                                                                                                                                                                                                                                                                                                                                                                                                                                                                                                                                                                                                                                                                                                    |
|---------------------------------------------|--------------------------------------------------------------------------------------------------------------------------------------------------------------------------------------------------------------------------------------------------------------------------------------------------------------------------------------------------------------------------------------------------------------------------------------------------------------------------------------------------------------------------------------------------------------------------------------------------------------------------------------------------------------------------------------------------------------------------------------------------------------------------------------------------------------------------------------------------------------------------------------------------------------------------------------------------------------------------------------------------------------------------------------------------------------------------------------------------------------------------------------------------------------------------------------------------------------------------------------------------------------------------------------------------------------------------------------------------------------------------------------------------------------------------------------------------------------------------------------------------------------------------------------------------------------------------------------------------------------------------------------------------------------------------------------------------------------------------------------------------------------------------------------------------------------------------------------------------------------------------------------------------------------------------------------------------------------------------------------------------------------------------------------------------------------------------------------------------------------------|

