| Outcomes:     | 
Primary Outcome
 
 
- Sensitivity and specificity of HPV test followed by VIA/VILI to detect cervical precancerous lesions in sub-Saharan Africa using histology as gold standard
 
 
Secondary outcomes
 
 
- Provide teaching material for training health care professionals on cervical cancer prevention through VIA/VILI (cervical images database), Sexual dysfunction score, score of anxiety and method of contraception after screening procedures,
 
- Willingness to participate in the 3T screening program,
 
- Prevalence of HPV infection, cervical pre-cancer and cancer,
 
- HPV clearance measured by self HPV at 6 and 12 months follow up,
 
- Prevalence of CIN2+ disease at the 12-month follow-up,
 
- Acceptability of self-HPV test, thermal ablation and cervical cancer screening procedures,
 
- Women's experiences and attitudes on cervical cancer screening
 
- Proportion of side effects and complications after thermal ablation or LEEP,
 
- VIA test-positivity rate (HPV-positive women);
 
- VIA test-positivity rate at 1- year follow-up of VIA-negative tests
 
- Thermal ablation efficacy
 
- Increase awareness on gynecological pathologies, including cervical
 
                                                                                                                                                                                                                                                                                                                                                                                                                                                                                                                                                                                                                                                                                                                                                                                                    |

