| Measurements and Procedures: | 
Primary (Flow chart)
 
 
- After a community-based sensitization campaign, participants will undergo HPV-testing with GeneXpert® machines using self-collected samples (Flocked swabs) transported in a 0.9% sodium chloride (NaCl 0.9%) medium,
 
- HPV-negative women will be reassured and advised to do the next screening 5 years later,
 
- HPV-positive women will undergo the following sequence on the same day: VIA/VILI > Pap smear > Cervical Biopsy (VIA-guided biopsy for VIA-positive participants and random biopsy for VIA-negative participants) > Endocervical Curettage (ECC). All participants with a positive VIA/VILI will be treated with thermal ablation if eligible or Loop Electrosurgical Excision Procedure ((LEEP) for participants ineligible for thermal ablation).
 
- Specimens of Pap smear will be transported in BD SurePath™ vials (Becton Dickinson Company, Franklin Lakes New Jersey, USA) or ThinPrep™ (Hologic, Bedford, MA, USA) while those of biopsy, LEEP and ECC will be transported separately in formol (formaldehyde solution) vials.
 
- VIA/VILI will be interpreted on Smartphone images according to ABCD criteria and compared to VIA.
 
- Results of cytological and histological analysis will be disclosed to participants by midwives or obstetrician-gynecologist. Those requiring additional treatment will receive it for free.
 
- Follow-up visits will be organized 6 and 12 months later for women having received a treatment (self HPV GeneXpert® test > VIA/VILI > Pap smear > Guided biopsy + ECC).
 
 
Follow-up visits will be organized 12 months later for women having a positive screening test but VIA/VILI negative (self HPV GeneXpert® test > VIA/VILI > Pap smear > Guided biopsy + ECC)
 
Secondary
 
 
- Pictures of the cervix (native, after application of acetic acid (VIA) and lugol's iodine (VILI)) will be taken using a Smartphone (Samsung Galaxy™ S5). In addition to these 3 pictures, a 120 second long video of the cervix (120 images) will be recorded during the VIA. Then a database will be built-up.
 
- During the visit, participants will receive information on gynecological pathologies, including cervical cancer, sexually transmitted diseases and HIV, vaginal fistula
 
- All participants diagnosed with pre-cancer or cancer of the cervix will receive free of charge treatment
 
- Participants treated by thermal ablation and an equivalent number of untreated patients (about 250 in each group) will be followed up by phone or interview for a survey on fertility and obstetrical
 
 |

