| Nombre participants justificatif: | de et    | 
Nous incluons 6000 participantes. Avec une prévalence d'infection à HPV supposée de 20% nous nous attendons à 1200 participants HPV+.
 
Parmi ces 1200 participantes HPV+, 120 auront des lésions intra épithéliales de haut grade (CIN2+) en considérant une prévalence de 10% de CIN2+ chez les HPV+. En supposant un taux de pertues de vue de 20%, 96 cas de CIN2+ seront analysés pour déterminer la sensibilité de l'IVA (estimée à environ 60%) avec une précision de +/- 9,8%.
 
Parmi ces 1200 participantes HPV+, 1080 n'auront pas de lésions CIN2+. Si le taux de pertues de vue est de 20%, 864 cas sans lésions CIN2+ seront analysés pour déterminer la spécificité de la VIA (estimée à environ 50 %) avec une précision de +/-3,3%.
 |
| Durée de l'étude:                 |                 | 72 mois                                                                                                                                                                                                                                                                                                                                                                                                                                                                                                                                                                                                                                                                                                                                                               |
| Planification de l'étude:         | de       | 
Recrutement de la première patiente : Septembre 2018
 
Recrutement de la dernière patiente : Septembre 2024
                                                                                                                                                                                                                                                                                                                                                                                                                                                                                                                                                                                                                                               |

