### 5.2.2 Secondary endpoint/outcomes

- Provide teaching material for professional training on cervical cancer prevention through VIA/VILI (cervical images database)
- Sexual dysfunction score, score of anxiety and method of contraception after screening procedures
- Willingness to participate in the 3T screening program;
- Prevalence of HPV, cervical pre-cancer and cancer among Cameroonian women
- HPV clearance at 6 and 12 months follow up
- Prevalence of CIN2+ disease at the 12-month follow-up
- Acceptability of self-HPV test, thermal ablation and cervical cancer screening procedures
- Women's experiences and attitudes on cervical cancer screening
- Proportion of side effects and complications after thermal ablation or LEEP
- VIA test-positive rate (HPV-positive women);
- VIA test-positive rate after 1- year follow-up of VIA-negative tests
- Thermal ablation efficacy
- Increase awareness on gynecological pathologies, including cervical cancer, sexually transmitted diseases and HIV, vaginal fistula in the community of the study area
- Number of women screened with and without the participation of community health care workers.
- Specificity and sensitivity of the AVC test, using histology as the reference standard
- Acceptability of the AVC test

The demand for programs to control CC in low-resource settings is strong. Lessons that we have learned from our previous experience, combined with results of recent researches have put our group in an excellent position to identify innovative and cost-effective strategies for reducing CC morbidity and mortality in developing countries. The obtained data will determine the level of support, which will be needed to maintain high-quality CC prevention services in equipment and provider skills. We expect also that our data will also determine how a CC- screening program might be established in a sustainable prevention strategy.

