#### **Post treatment Visit (follow up at 6 and 12 months)**

- Treated patients will be seen at 6 and 12 months post-treatment visits, where they will perform self-HPV GeneXpert® test followed by VIA/VILI, Pap smear, Cervical Biopsy and ECC.
- Participants who will become pregnant during the study shall be counselled on risks excluded from the study and offered focalized antenatal and post-partum care.
- Data on women's quality of life and methods of contraception after screening procedures will be collected according to validated questionnaire;
- Participants treated by thermal ablation and an equivalent number of untreated patients (about 250 in each group) will be followed up by phone or interview for a survey on fertility outcomes. Participants from a previous study on cervical screening in Dschang, conducted by our study group, will be contacted as well for this follow-up study (about 50 in each group). Information about obstetrical outcomes may also be retrieved from medical records.

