## **8.3 Assessment of secondary endpoint/ outcomes**

In the conditions cited above, women with suspected precancerous lesions following VIA/VILI, will be immediately treated. The personnel will be trained to recognize fistulas. Patients with a fistula, will be transferred to the University Teaching Hospital of Yaoundé and will be treated free of charge. Voluntary women will be addressed to the HIV department for screening and free treatment. The feasibility of a prevention program for cervical cancer, sexually transmitted diseases and obstetrical fistula, will be assessed by the local teams in Cameroon and the University hospital of Geneva.

The University Hospital of Geneva will invest in the development of a consultation room in the district hospital of Dschang, with the purchase of a gynecologic table, a colposcope and initial renewable material. The GeneXpert® machine is already available in Dschang. Geneva will also insure the training of the medical team including nurses, one medical technician and CHWs, and the salary and/or financial compensations of this team during the 72-month study period. This team will then be supervised by a part-time gynecologist.

At the end, an activity report will allow us to evaluate the efficiency of the advertisement campaign, the number of screened women, and ability of the Ministry of Health to take over the fees of the material and human resources to carry on with the promotion of women health.

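### The stated dates leave no follow-up time after the last recruitment, so, read literally, HPV-positive women enrolled in the final 12 months cannot supply the 12-month secondary outcomes within the 72-month study.

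*Protocol*

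**What the plan says.** The English synopsis, under Study Schedule, has "Month Year of First-Participant-In (planned): September 2018" and "Month Year of Last-Participant-In/Out (planned): September 2024", with a study duration of 72 months. The French synopsis gives the same duration and start, and for the end it names recruitment explicitly: "Recrutement de la dernière patiente : Septembre 2024". Section 8.3 repeats the duration when it commits to training and paying the team "during the 72-month study period".

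Follow-up is laid down in two places. The post-treatment visit section says: "Treated patients will be seen at 6 and 12 months post-treatment visits". The English synopsis adds: "Follow-up visits will be organized 12 months later for women having a positive screening test but VIA/VILI negative". HPV-negative women have no study visit at 6 or 12 months; they are advised to be screened again after 5 years.

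Several secondary outcomes rest on those visits: "HPV clearance measured by self HPV at 6 and 12 months follow up" (synopsis), prevalence of CIN2+ at 12 months, and "VIA test-positive rate after 1- year follow-up of VIA-negative tests" (section 5.2.2).

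The timeline in section 1 has separate rows for the screening campaign, the 6-month visits and the 12-month visits. Its last columns are 09/20-09/23, 09/23-09/24, 10-12/24 and 01-02/25. In the text available for this review the cells are empty, so the timeline does not show which activity falls in which period.

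**The concern.** The duration equals the interval from first entry to last entry exactly. A woman recruited in the last stated month reaches month 12 a year after the study has ended, and the timeline closes before she reaches even month 6. The English field could be read as an end-of-study date, but the French wording names recruitment.

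At stake is the amount of information behind the 6- and 12-month secondary outcomes. Women who enter late would be cut off by the calendar, not by their own withdrawal. Section 8.3 funds the team only for the 72 months, so visits after September 2024 have no stated staffing either.

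**Working it through.** **1. The stated duration.** September 2018 to September 2024 = 6 × 12 = 72 months. The plan's figure reproduces, with no month left over.

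**2. Time needed against time available.**

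| Interval | Months |
|---|---|
| Last in to last out, as stated | 0 |
| Last in (09/24) to end of last timeline column (02/25) | 5 |
| Needed, treated women | 6 and 12 |
| Needed, HPV-positive and VIA/VILI-negative women | 12 |

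With last-in at September 2024, the last 12-month visit falls in September 2025, and the study lasts 72 + 12 = 84 months. With last-out held at September 2024, recruitment has to end by September 2023: 60 + 12 = 72.

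**3. How many women.** Inputs from section 9.1: 6000 women, 20% HPV-positive, CIN2+ in 10% of these, expected sensitivity 60% and specificity 50%. The accrual pattern is not stated, so it is an assumption here.

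- HPV-positive: 6000 × 0.20 = 1200.
- VIA-positive share of the HPV-positive: 0.10 × 0.60 + 0.90 × 0.50 = 0.51.
- Share enrolled in the final 12 months, for uniform accrual over L months ending September 2024: 12/L.

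| Accrual assumption | Share | HPV-positive without month 12 | VIA-positive | VIA-negative | Treated, also without month 6 |
|---|---|---|---|---|---|
| L = 72 | 16.7% | 200 | 102 | 98 | 51 |
| L = 60 | 20% | 240 | 122 | 118 | 61 |
| L = 48 | 25% | 300 | 153 | 147 | 77 |
| Recruitment ends by 09/23 | 0% | 0 | 0 | 0 | 0 |

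The last column is half of the VIA-positive column, since under uniform accrual half of the final-year women enter in the last 6 months. It takes VIA-positive women as treated on the day of screening. If visits continued to February 2025, the last 7 months of enrolment would still miss month 12: 7/72 = 9.7%, about 117 of 1200.

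**4. Effect on precision of a 12-month proportion.** Losing 16.7% widens a confidence interval by 1/√(1 − 0.167) = 1.095, about 10%.

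**5. The primary endpoint.** VIA/VILI, biopsy and endocervical curettage are done on the day of screening, so accuracy against histology needs no later visit. The stated precision reproduces: 1.96 × √(0.6 × 0.4/96) = 9.8% and 1.96 × √(0.5 × 0.5/864) = 3.3%. Neither figure depends on the end date.

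**The case against.** The best defence is that this is a date label and not a defect of design. The combined English field can be taken as the end of the study, which agrees with 72 months. The timeline breaks at 09/23, which would suit recruitment to that month and a year of follow-up, and the cell content that would settle the matter is not readable here. Cut-off by enrolment date also need not bias a 12-month proportion unless risk changes over calendar time; at the 16.7% loss it mainly widens intervals by about 10%, and only for secondary outcomes that carry no sample-size target of their own.

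Much of this stands, and it limits the size of the point. It does not remove it: the French synopsis says recruitment, no text gives September 2023, and the two synopses cannot be followed as written together with the visit schedule.

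Stronger readings are tempting and are not supported:

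- A reader might infer that all final-year women are affected, about 1000 of 6000 under uniform accrual. About 800 of these would be HPV-negative and have no scheduled follow-up; the relevant number is about 200.
- A reader might infer that half of those affected also miss month 6. That visit applies to treated women only, so the figure is about 51.
- A reader might combine the end date with the rule in section 9.3.1 that complete electronic case report forms are analysed, and conclude that late women leave the primary analysis. The protocol does not say that a form without a 12-month page is incomplete.
- A reader might add the loss to the 20% drop-out. Section 9.1 applies that 20% to the baseline accuracy sample and does not present it as attrition at month 12.

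**Conclusion.** The schedule is wrong as written and should be corrected. On the stated dates there are 0 months between last entry and last exit where 12 are needed, and 5 months to the end of the timeline. That part is calendar arithmetic and rests on no assumption beyond reading the French recruitment date at its word.

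The number of women affected does rest on an assumption, because accrual is not stated: 17% of the HPV-positive women (about 200 of 1200) if uniform over 72 months, 20% or 25% if recruitment is confined to the last 60 or 48 months, and none if it ends by September 2023. The split into 102 VIA-positive and 98 VIA-negative women also uses the protocol's own expected sensitivity, specificity and CIN2+ prevalence.

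The outcomes concerned are HPV clearance (at 12 months, and at 6 months for the latest treated women), 12-month CIN2+ prevalence and 1-year VIA positivity. All are secondary. The documents do not show bias in them or an unusable endpoint, and the primary sensitivity and specificity keep their stated precision.

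**What to change.** State last participant in and last participant out as two separate dates in both synopses, and make them agree with the section 1 timeline and with the 72 months. There are two consistent ways:

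- Last-in no later than September 2023 and last-out September 2024, keeping 72 months. At the 30 women per day given in section 7, 6000 women need 6000/30 = 200 screening days, so an earlier close looks feasible on the protocol's own capacity figure. The cost is a shorter recruitment window.
- If recruitment does run to September 2024, move last-out and the data analysis to after September 2025 and restate the duration as about 84 months in the English synopsis, the French synopsis and section 8.3. The cost is a longer stated study, with team funding to match.

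If September 2023 was always intended, the amendment only corrects the French recruitment date and splits the English field, and no loss of 12-month data is expected from the calendar.
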